**12.2 Special Event Data**

A Special Event form will require completion for every hospitalization and death. The primary and secondary diagnosis for each hospitalization will be recorded in patients who suffer an adverse event. Detailed information will be collected for the death of every patient including the review of death certificates.

**13.0 Central Adjudication of all Events**

All suspected treatment related morbid events or deaths will be reviewed blind to the treatment group by the Events Adjudication Committee. This will be done every 6 months for the following events: (1) death classified by cause; (2) toxicities related to chemotherapy, radiation, or surgery; (3) all hospitalizations.

**14.0 Adverse Events and Safety**

**14.1 Adverse Event Reporting**

Any fatal (grade 5) or life-threatening (grade 4) adverse reaction that is due to or suspected to be the result of protocol treatment must be reported to the Clinical Trials Group Chairperson by telephone within 24 hours of discovery. Unknown adverse reactions (> grade 2) must be reported to Clinical Trials Group and the local IRB within 10 working days of discovery. Reactions thought not to be treatment related should not be reported; however, a report should be made if there is a reasonable suspicion that the effect is due to protocol treatment.

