**11.2 Secondary Outcomes**

**11.2.1 Survival at 5 years.** All patients will be followed every 3 months for 2 years and then every 6 months up to 5 years or until death if it occurs before 5 years. Survival will be measured from randomization.

**11.2.2 Disease Free Survival.** Recurrence rates in the two groups including local (gastric or esophageal bed), regional (regional lymph nodes), and distant recurrences (supraclavicular lymph node, liver, peritoneal carcinomatosis, or lung, brain, etc.) will be compared. Disease free survival will be measured as the time from patient entry onto study until the first malignant disease recurrence.

**11.2.3 Site of Treatment Failure.** The location of the first site of malignant disease recurrence will be recorded. Local failure occurs within the gastric or esophageal bed, or regional lymph nodes. Distant failure occurs in the supraclavicular lymph nodes, liver, peritoneal carcinomatosis, pleura, lung, bones, brain, or elsewhere not considered local.

**11.2.4 Toxicities**. Possible adverse drug or radiation events will be reported as described in the London Regional Cancer Program Patient Assessment Record (PAR).

**11.2.5 Completeness of Resection.** The number of R0, R1, R2, and unresectable patients will be compared.

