**21.0 Limitations, Potential Pitfalls and Strategies**

Assessment bias always occurs in oncology trials because it is often impossible and impractical to blind the outcome assessment. This bias that may occur with quality-of-life instruments but can be minimized by using the self-administrated instruments that makes physician and data technician blinding unnecessary. This concern is not a problem when survival is a secondary outcome, as it is in this trial. The other outcomes could be blinded but are secondary questions and will be used for hypothesis generating. The added cost is not justified. Selection bias will be minimized by randomization just after the eligibility visit. All eligible, non-randomized patients will be recorded and used later in sensitivity analyzes. Crossovers between treatment arms will not be allowed.

New information may become available supporting combined modality therapy prior to completion of the trial. This may make it unethical to continue with the protocol. It would be unusual for clinical practice to drastically change based on the results of one or maybe two trials. Confirming evidence is always needed to support the results. We are not aware of any trial currently evaluating preoperative versus postoperative chemoradiation for resectable esophageal cancer.

Technical advances in the field, such as newer approaches to surgery, radiation, and newer chemotherapeutic agents could make the current approach archaic before the trial is completed, but this is very unlikely. The London surgeons are already performing minimally invasive esophagectomies and are the current leaders in Canada. The participating surgeons have agreed on the proposed surgical technique, are comfortable and have experience with it. We anticipate that it will remain the standard for at least a decade. Minor changes in the field will be incorporated into the procedure at a national level to remain current and provide state-of-the-art care.

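### The safety sections define different event sets: the toxicity outcome leaves out surgical events in a way that differs by arm, and unblinded attribution filters some events before blind review

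*Protocol*

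**What the plan says.** Six places in the protocol bear on which safety events are recorded, reviewed and compared.

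- **Section 3.2.1** sets a secondary objective of comparing both the toxicity and the morbidity of the two strategies.
- **Section 11.2.4** gives the matching outcome: "Possible adverse drug or radiation events will be reported" by way of the cancer centre's Patient Assessment Record (PAR). No item from 11.2.1 to 11.2.6 names surgical morbidity.
- **Section 12.1** schedules toxicity and morbidity data at baseline and every two months to one year. It states no attribution filter and does not define morbidity.
- **Section 12.2** is unconditional: "A Special Event form will require completion for every hospitalization and death".
- **Section 13.0** opens with "All suspected treatment related morbid events or deaths will be reviewed blind to the treatment group by the Events Adjudication Committee". Its heading nevertheless speaks of all events. Its list covers deaths by cause, toxicities of chemotherapy, radiation or surgery, and all hospitalizations.
- **Section 14.1** ties rapid notification of grade 4 and 5 events to attribution ("adverse reaction that is due to or suspected to be the result of protocol treatment must be reported to the Clinical Trials Group Chairperson") and adds: "Reactions thought not to be treatment related should not be reported". It makes an exception where treatment is reasonably suspected.

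On blinding, section 17.2 says that patients, investigators and data analysts were all unblinded. Section 21.0 says of outcomes other than quality of life and survival: "The other outcomes could be blinded but are secondary questions and will be used for hypothesis generating". It then rejects the extra cost.

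**The concern.** The trial compares two orders of the same modalities, so a fair safety comparison has to count the same kinds of event from the same starting point in both arms. Two features work against that.

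First, an outcome confined to drug or radiation events depends on what the patient has already received. Because the order of treatment differs by arm, the same operative complication can be eligible in one arm and ineligible in the other.

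Second, blind adjudication protects against biased attribution only for events that reach the committee. If an unblinded clinician must first suspect treatment, the blinding comes after the judgement it was meant to protect.

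At stake is the comparison in objective 3.2.1: recorded toxicity could differ between arms without any true difference. Staff following different sections could also record different event sets.

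**Working it through.** **Step 1. Timing of surgery relative to drug and radiation.** In the control arm, chemoradiation precedes surgery (section 7.1), so a postoperative complication occurs in a patient already exposed and can be called a possible drug or radiation event. In the experimental arm, chemotherapy begins 8 to 12 weeks after surgery (section 9.0, Arm II). Section 10.0 does not offer adjuvant therapy to resected pT1N0 and pT2N0 patients, although section 8.2.5 asks that it be considered if margins are positive. Any complication before adjuvant therapy starts, and any complication at all in a patient who never receives it, cannot be a drug or radiation event. This follows from treatment order and needs no assumed rate.

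**Step 2. Each type of event against each rule.**

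| Event | 12.2 form | 13.0 opening sentence | 13.0 list | 14.1 report | 11.2.4 outcome |
|---|---|---|---|---|---|
| Death | Always | Only if suspected | Yes | Only if suspected | Only if possibly drug or radiation |
| Hospitalization | Always | Only if suspected | Yes | Only if suspected and of reportable grade | Only if possibly drug or radiation |
| Operative complication, control arm | If hospitalized or fatal | If suspected | Yes, as surgical toxicity | If suspected and of reportable grade | Can count |
| Operative complication before adjuvant therapy, experimental arm | If hospitalized or fatal | If suspected | Yes, as surgical toxicity | If suspected and of reportable grade | Cannot count |
| Non-fatal event without hospitalization, judged unrelated | No | No | No | No | Unclear: collected under 12.1, but the outcome is limited to possible drug or radiation events |

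Two conflicts can be read off. Section 13.0 disagrees with itself on deaths and hospitalizations, since its opening sentence is narrower than its list. Section 11.2.4 disagrees with 3.2.1 and with the 13.0 list on surgical events. A third lies outside the table: 13.0 prescribes review blind to arm, while 21.0 treats blinding of such outcomes as not worth its cost.

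**Step 3. How much could an attribution filter matter?** The protocol states no adverse-event rate or attribution probability for this trial, so there is no figure to reproduce. The following is an illustration on assumed values. Let the true event rate be *p* in both arms, with *n* = 48 per arm (section 17.1), and let the probability that an event is attributed to treatment be *a* = 0.9 in one arm and *b* in the other.

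- Recorded rates: p1 = p·a and p2 = p·b, so the spurious difference is d = p(a − b).
- With p̄ = (p1 + p2)/2, the standard error under the null is se0 = √[2p̄(1 − p̄)/n].
- The actual standard error is se1 = √{[p1(1 − p1) + p2(1 − p2)]/n}.
- False-positive rate at two-sided 0.05: Φ[(d − 1.96·se0)/se1] + Φ[(−d − 1.96·se0)/se1].

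For p = 0.40 and b = 0.7: p1 = 0.36, p2 = 0.28, d = 0.08 and p̄ = 0.32. Then se0 = √(0.4352/48) = 0.0952 and se1 = √(0.432/48) = 0.0949. The two terms are Φ(−1.12) ≈ 0.131 and Φ(−2.81) ≈ 0.002, in total 0.133.

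| True rate | b = 0.9 | b = 0.8 | b = 0.7 | b = 0.5 |
|---|---|---|---|---|
| 20% | 0 points, 5% | 2 points, 5.8% | 4 points, 8.3% | 8 points, 20.2% |
| 40% | 0 points, 5% | 4 points, 7.0% | 8 points, 13.3% | 16 points, 41.4% |
| 60% | 0 points, 5% | 6 points, 9.0% | 12 points, 21.6% | 24 points, 66.8% |

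The table shows that unequal attribution can matter. It does not show that it occurs here.

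**The case against.** The strongest reply is that section 14.1 is a notification rule: it sets who is told and how fast. The data for comparison come from elsewhere. The PAR is completed in part at the eligibility visit for baseline toxicity (section 6.3), before any protocol treatment, so it is not confined to attributed events. Section 12.1 collects toxicity and morbidity on a schedule with no stated filter. Surgery is also part of protocol treatment in both arms, so a suspected operative complication falls within 14.1 and item 2 of the 13.0 list, and one during an admission is covered by the 12.2 form.

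Most of this stands, and it rules out some stronger readings:

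- A reader might infer that no event is reported or adjudicated unless treatment is suspected. Section 12.2 and the 13.0 list contradict that for every death and hospitalization.
- A reader might infer that the whole safety comparison rests on biased attribution. Given the PAR and section 12.1, the documents do not show this.
- A reader might size the problem from the 6.7% postoperative mortality in the Introduction (0.067 × 48 = 3.2 deaths per arm). Deaths are captured regardless of attribution, and that figure comes from a meta-analysis of preoperative chemotherapy against surgery alone, so it does not measure this gap.
- A reader might fault 14.1 for naming the local IRB only for unknown reactions ("Unknown adverse reactions (> grade 2) must be reported to Clinical Trials Group and the local IRB within 10 working days of discovery"). Treating known and unknown reactions differently is not a contradiction, and it has no bearing on the comparison between arms.

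The reply does not remove two things. The outcome named for comparison is still 11.2.4, which leaves out surgery whatever is collected elsewhere. And the opening sentence of 13.0 still applies an unblinded filter ahead of a blind committee.

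**Conclusion.** The concern holds as an inconsistency in how the safety event set is defined. Sections 11.2.4, 13.0 and 14.1 do not agree with one another or with 3.2.1, 12.1 and 12.2. Taken literally, 11.2.4 excludes operative complications before adjuvant therapy in the experimental arm and admits similar ones in the control arm. That conclusion rests only on the stated treatment order. How often clinicians would attribute operative complications to chemoradiation in the control arm is unknown.

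The attribution filter is a narrower gap, confined to non-fatal events without hospitalization that are judged unrelated. Its size cannot be derived from the protocol. Over the assumed values with unequal attribution, the spurious difference runs from 2 to 24 percentage points.

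Severity is moderate. Safety is a secondary objective, section 17.2 says the trial is not powered for secondary outcomes, and the primary FACT-E comparison is unaffected.

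**What to change.** 1. **Section 11.2.4:** add surgical complications. Count grade 3 to 5 events from randomization in both arms regardless of attribution, with attribution recorded in a separate field. The outcome then matches objective 3.2.1.
2. **Section 13.0:** replace the opening sentence with one intake rule that matches the heading and list: all deaths and hospitalizations from the 12.2 forms, plus grade 3 to 5 toxicities including surgical ones. Align the blinding statement in section 21.0 with the blind review prescribed here.
3. **Section 14.1:** state that the sentence on unrelated reactions governs expedited notification only and does not limit what is recorded for the outcome comparison.

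The cost is mainly wording, using the existing forms and committee. There will be somewhat more event recording and committee review, and recorded event rates will look higher.

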**15.0 Management of Intercurrent Events**

Several illnesses and major events may befall patients during the study. Referring physicians are free to treat each patient according to their best judgement. However, when in doubt they are encouraged to discuss an individual's management with the Thoracic Clinical Trials Centre.

The clinical course of esophageal cancer one in which a significant number of patients treated with standard therapy will deteriorate or die. Significant deterioration may be in the form of worsening symptoms of dysphagia, pain, anorexia, weight loss due to disease progression. The treating oncologist should always use the most appropriate management that is in the best interest of the patient.

**15.1 Ancillary Therapy**

Patients should receive full supportive care, including transfusions of blood and blood products, erythropoietin, antibiotics, antiemetics, etc., when appropriate. Filgrastim (G-CSF) and sargramostim (GM-CSF) treatment is discouraged. They may not be used prophylactically to avoid dose reductions or delays.

**15.2 Other Agents**

Treatment with hormones or other chemotherapeutic agents may not be administered except for steroids given for adrenal failure; hormones for non-disease related conditions (e.g., insulin for diabetes); and intermittent use of dexamethasone as an antiemetic.

**15.3 Nutrition**

All patients undergoing preoperative chemoradiation (Control Arm) will undergo the insertion of a percutaneous feeding gastrojejunostomy for enteral nutritional support. Patients undergoing postoperative chemoradiation will have a surgically placed feeding jejunostomy for supplemental nutrition as needed.

**16.0 Participant Safety and Confidentiality**

The study physicians will be responsible for the safety or participants under his or her care. The Steering Committee will have primary responsibility for the monitoring of study data for adverse trends and morbidity. The confidentiality of all participants will be protected both at the study site and the Study Coordinating and Methods Center. Completed data collection forms will receive the same protection as other medical records. Reporting of study results will not identify individual patients.

**17.0 Sample Size Determination**

**17.1 Sample Size**

The sample size is based on an improvement in the quality-of-life as measured by the FACT-E at one year. If we assume an improvement in the treatment arm of 15 points, 2- sided α=0.05, β= 0.2 and σ=25 (28)

Formula:

n per group = (Z_α_ + Z_β_)^2^ *2σ^2^

Δ^2^

σ=25

Δ=15

n=44 per arm.

**Summary of Sample Size Estimates**

| **σ** | **Δ** | **α** | **β** | **n**  **(each arm)** | **Add 10%** | **Total N** |
| --- | --- | --- | --- | --- | --- | --- |
|  |  |  |  |  |  |  |
| 25 | 10 | 0.05 | 0.2 | 98 | 108 | 216 |
| 25 | 15 | 0.05 | 0.1 | 58 | 64 | 128 |
| **25** | **15** | **0.05** | **0.2** | **44** | **48** | **96** |
| 25 | 20 | 0.05 | 0.1 | 33 | 36 | 72 |
| 25 | 20 | 0.05 | 0.2 | 25 | 27 | 54 |
| 25 | 25 | 0.05 | 0.1 | 21 | 23 | 46 |
| 25 | 25 | 0.05 | 0.2 | 16 | 17 | 34 |

The sample size was estimated based on an improvement in the HRQOL as measured by the FACT-E at one year of 15 points in the Neoadjuvant arm compared to the Adjuvant arm. Based on a two-sample t-test, using 2-sided testing, alpha = 0.05, power = 80% and standard deviation = 25, 48 patients would be required in each arm (96 total patients) after adjusting for 10% lost to follow-up (32). The randomization was completed according to a computer-generated randomization list by an independent statistician who had no clinical involvement in the trial and then allocated by the Thoracic Clinical Trials office to ensure concealment of the randomization process (33). Patients were randomized in a 1:1 allocation ratio and stratified by nodal status and surgeon.

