Our own phase II data suggested that postoperative chemoradiation may be beneficial for esophageal cancer patients (10). Thirty-eight lymph node positive (N1) patients underwent esophagectomy followed by postoperative chemotherapy (cisplatin, 5-FU, + epirubicin) and 50 Gy radiotherapy (CRT) and 28 (N1 patients) underwent surgery alone (S). Pre-operative risk factors, tumour characteristics, ECOG scores and lengths of stay were similar. Disease-free survival was similar (CRT 10.2 months vs. S 10.6 months) but the surgery alone group had more local recurrences (CRT 13% vs. S 35%). Overall Kaplan-Meier survival analysis showed a significant advantage with postoperative chemoradiation (log rank p=0.001). The median overall survival for the chemoradiation group was 47.5 months which was significantly longer than the surgery alone group (14.1 months). The three-year survival was 62% in the CRT group and 25% in the S group, and the five-year survival was 48% and 0% respectively.

Rice and colleagues from the Cleveland Clinic compared 31 patients with locoregionally advanced esophageal cancer (90% pT3, 81% pN1, and 13% pM1a) that received postoperative adjuvant chemoradiotherapy after resection to 52 patients that underwent esophagectomy alone (11). Patients received 50.4 to 59.4 Gy external beam radiation with concurrent two 4-day cycles of intravenous 5-fluorouracil (1,000 mg/m2/d) and cisplatin (20 mg/m2/d) during the first and fourth week of adjuvant therapy. Among propensity-matched patients, median, 1-year, and 4-year survivals for those receiving adjuvant therapy versus esophagectomy were 28 versus 15 months, 60% + 11% versus 65% + 11%, and 44%+11% versus 0% (P=0.05). Median time to recurrence was 25 versus 13 months (P =0.04), and recurrence-free survival was 22 versus 10 months (P=0.02). The authors concluded that patients with locoregionally advanced carcinoma after esophagectomy should be considered for adjuvant therapy.

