**2.0 Hypothesis**

Postoperative cisplatin, 5-FU, and epirubicin chemotherapy with concurrent extended volume radiotherapy following surgical resection is superior to standard preoperative cisplatin and 5-FU chemotherapy plus radiotherapy followed by surgical resection for resectable esophageal carcinoma.

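### The sample-size paragraph puts the expected gain in the control arm, and its 80% power makes no allowance for deaths before the one-year FACT-E score

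*Protocol*

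**What the plan says.** Section 17.1 sets the basis: "The sample size is based on an improvement in the quality-of-life as measured by the FACT-E at one year". Its assumptions follow: "If we assume an improvement in the treatment arm of 15 points, 2- sided α=0.05, β= 0.2 and σ=25". The formula there gives 44 per arm, and the table under Summary of Sample Size Estimates adds 10% to reach 48.

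The paragraph below that table names the test ("Based on a two-sample t-test, using 2-sided testing, alpha = 0.05, power = 80% and standard deviation = 25") and concludes that "48 patients would be required in each arm (96 total patients) after adjusting for 10% lost to follow-up". It describes the planned effect as a gain of "15 points in the Neoadjuvant arm compared to the Adjuvant arm".

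Four other places bear on this:

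- Section 2.0 hypothesises that the postoperative regimen "is superior to standard preoperative cisplatin and 5-FU chemotherapy plus radiotherapy followed by surgical resection".
- Section 7.1 names induction (preoperative) treatment as the control arm and surgery followed by postoperative treatment as the experimental arm.
- Section 17.2 says that missing values are neither imputed nor replaced.
- Section 15.0 expects an appreciable share of patients on standard treatment to worsen or die.

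**The concern.** The direction of the planned effect is stated in two incompatible ways for the primary endpoint. A reader of the sample-size paragraph would think the trial was planned to show a benefit of the control strategy. A reader of the hypothesis would think the reverse.

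The second issue is the meaning of the 80%. The comparison that was powered needs a FACT-E score at 12 months. A patient who has died has no such score, and nothing is put in its place. The only allowance is 10%, described as loss to follow-up. If deaths in the first year come on top of that, or exceed it by themselves, fewer than 44 per arm enter the test and the true power is below the stated figure. A null primary result would then be read as stronger evidence against a 15-point difference than the design can supply.

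**Working it through.** **Direction.** The statements side by side:

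| Place | Arm expected to do better |
|---|---|
| Section 2.0 | Postoperative (adjuvant) |
| Section 17.1 | The treatment arm; by the labels of section 7.1 the experimental, postoperative arm |
| Paragraph under Summary of Sample Size Estimates | Neoadjuvant, which section 7.1 calls control |

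The third cannot stand with the first two. The formula uses the squared difference, the test is two-sided and allocation is 1:1, so swapping the arms leaves N and power as they are.

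**Reproducing the plan's figures.** Inputs from section 17.1: two-sided alpha 0.05, power 80%, SD 25, difference 15.

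- n per arm = (1.96 + 0.8416)² × 2 × 25² / 15² = 7.849 × 1250 / 225 = 43.6, rounded up to 44. This matches.
- Allowance: 44 × 1.1 = 48.4, taken as 48. Dividing instead, 44 / 0.9 = 48.9, or 49. The stated 48 is within one patient per arm.
- At exactly 10% loss, 48 × 0.9 = 43.2 per arm. Power is 79.6% by the normal approximation and 78.7% by the exact t-test.

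**Adding deaths.** Let f be the total fraction without a one-year score, from death or loss. Then m = 48 × (1 − f) per arm are evaluable. Power comes from the noncentral t with noncentrality (15/25) × √(m/2) and 2m − 2 degrees of freedom. The protocol gives no f, so the values below are assumptions.

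| f | Evaluable per arm | Power, normal | Power, exact t |
|---|---|---|---|
| 10% | 43.2 | 79.6% | 78.7% |
| 15% | 40.8 | 77.3% | 76.3% |
| 20% | 38.4 | 74.8% | 73.7% |
| 25% | 36.0 | 72.1% | 70.9% |
| 30% | 33.6 | 69.1% | 67.8% |
| 40% | 28.8 | 62.4% | 60.9% |

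**Where the range comes from.** Section 1.0 cites outcomes in other cohorts. Where one-year survival is not reported, I convert by assuming exponential survival.

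- Investigators' phase II series, chemoradiation group, median 47.5 months: 1 − 0.5^(12/47.5) = 16% dead at one year.
- Gastric cancer trial, chemoradiotherapy group, median 36 months: 1 − 0.5^(12/36) = 21%.
- Cohort with 70% three-year survival: 1 − 0.70^(1/3) = 11%.
- Propensity-matched comparison, one-year survival reported directly as 60% and 65%: 40% and 35% dead.

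These figures show that 15% to 40% is a reasonable range to display. None of them is a forecast for this trial.

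**The case against.** Several points on the other side are fair.

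- **The direction error is harmless to the numbers.** This stands. A reader might infer that the sample size was computed for the wrong hypothesis and is invalid; it was not. Section 2.0 also names neither an endpoint nor 15 points, so it conflicts with the sizing paragraph on direction only.
- **The 10% loss alone does not break the 80%.** This stands too. A reader might infer from 48 × 0.9 = 43.2, which is below 44, that the plan fails on its own terms. The gap is one patient per arm and about one percentage point of power, which is rounding and no ground for action.
- **The cited survival figures do not describe this trial.** The 60% and 65% come from one matched comparison in more advanced disease (90% pT3, 81% pN1, 13% pM1a), and the 65% belongs to surgery alone, which is neither arm here. Section 5.1 requires M0, excludes biopsy-proven celiac and supraclavicular nodal metastases, and admits clinical N0 patients. A reader might infer that the protocol itself expects 35% to 40% to die within a year; it states no such rate. Other cited figures imply about 79% to 89% alive at one year. At 89% (42.6 evaluable per arm, with no other loss) power would be 78%.
- **The 10% may have been meant to cover deaths.** The table column gives no reason for the 10%, but the paragraph below it ties the allowance to loss to follow-up. Even if deaths were included, the most favourable of the conversions above (11%) already exceeds it.

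A reader might also multiply 40% deaths by a further 10% loss and quote a power of 56%. That takes the worst cited cohort and stacks a second assumption on it, so it is not a figure the documents support.

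**Conclusion.** Two points hold. The sample-size paragraph contradicts sections 2.0 and 17.1, read with section 7.1, on which arm is expected to gain; the effect is on interpretation only. The stated 80% also makes no provision for deaths before the one-year score, although the analysis uses only observed scores and the protocol expects deaths.

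The direction of the second error is clear, but its size is not fixed by the protocol. Over an assumed 15% to 40% without a one-year score, exact t-test power for 15 points with SD 25 runs from about 76% down to 61%, with 74% at 20% and 68% at 30%. These figures take the planned difference, SD, test and 48 per arm as given, and assume equal missingness in the two arms.

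**What to change.** - In the paragraph under Summary of Sample Size Estimates, state that the planned 15-point gain is in the adjuvant (experimental) arm, in line with sections 2.0 and 17.1.
- Replace the unqualified 80% with power for the number expected to have a 12-month FACT-E. Give the assumed fraction lost to death and follow-up together, label it as an assumption, and show the range (about 76% at 15%, 74% at 20%, 68% at 30%, 61% at 40%).

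Both are changes of wording. The sample size, treatment and visit schedule stay as they are, and no extra patients are needed. For scale only, keeping 44 evaluable would take 44 / 0.8 = 55 per arm at 20% and 44 / 0.6 = 73.3, or 74, at 40%. The cost is a less favourable stated power. A power figure adjusted for the baseline score should not be added on this basis, because the protocol gives no baseline correlation from which to calculate it.
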